## Abstract

**Introduction::**

Despite low mortality, cardiac surgery patients may experience serious life-threatening post-operative complications, often due to extracorporeal circulation and reperfusion. Miniaturised cardiopulmonary bypass (minimally invasive extracorporeal circulation) has been developed aiming to reduce the risk of post-operative complications arising with conventional extracorporeal circulation.

**Methods::**

The COMICS trial is a multi-centre, international, two-group parallel randomised controlled trial testing whether type II, III or IV minimally invasive extracorporeal circulation is effective and cost-effective compared to conventional extracorporeal circulation in patients undergoing elective or urgent coronary artery bypass grafting, aortic valve replacement or coronary artery bypass grafting + aortic valve replacement. Randomisation (1:1 ratio) is concealed and stratified by centre and surgical procedure. The primary outcome is a composite of 12 serious complications, objectively defined or adjudicated, 30 days after surgery. Secondary outcomes (at 30 days) include other serious adverse events (primary safety outcome), use of blood products, length of intensive care and hospital stay and generic health status (also at 90 days).

**Status of the trial::**

Two centres started recruiting on 08 May 2018; 10 are currently recruiting and 603 patients have been randomised (11 May 2020). The recruitment rate from 01 April 2019 to 31 March 2020 was 40-50 patients/month. About 80% have had coronary artery bypass grafting only. Adherence to allocation is good.

**Conclusions::**

The trial is feasible but criteria for progressing to a full trial were not met on time. The Trial Steering and Data Monitoring Committees have recommended that the trial should currently continue.

## Introduction

### Trial background

Despite decreasing mortality over the past decade, cardiac surgery patients may experience significant post-operative morbidity. Morbidity occurs because surgery itself carries a risk of iatrogenic harm, primarily as a result of ischaemia reperfusion injury (IRI)^
1
^ and the systemic inflammatory response (SIR).^
2
^ Although several strategies have been developed to reduce IRI and SIR (e.g. minimising the effects of perfusion and ‘conditioning’ the heart to make it more resistant to injury),^
3
^ these harms of surgery are often responsible for potentially life-threatening post-operative complications and delays in discharge from hospital.

Cardiac surgery with conventional extracorporeal circulation (CECC) provokes a vigorous SIR due to activation of stress pathways associated with post-operative end-organ complications (e.g. heart failure, renal impairment and neurological dysfunction). SIR is triggered by operative surgical trauma and IRI but is further exacerbated by the interaction of air, blood and synthetic components in the CECC apparatus. Minimally invasive extracorporeal circulation (MiECC) systems integrate contemporary innovations in CPB technology into a strategy which aims to reduce SIR and improve end-organ protection during cardiac surgery. They comprise a closed circuit with biologically inert blood contact surfaces and reduced priming volume; a centrifugal pump; a membrane oxygenator; a heat exchanger; a venous bubble trap or venous air removing device; a cardioplegia system and a shed-blood management device.^
4
^ Type IV hybrid modular MiECC systems (integrating a hard-shell venous reservoir as a stand-by component for immediate conversion to an open system) overcome safety concerns and unexpected intraoperative perfusion scenarios; thus, they are compatible with every cardiac surgical procedure.^
5
^

Four meta-analyses^6–9^ (with overlapping included RCTs; one also compared MiECC with off-pump coronary artery bypass grafting^
9
^ (CABG)) have reported substantial benefits of MIECC for 30-day mortality, stroke, myocardial infarction (MI), post-operative atrial fibrillation and renal dysfunction. No harms were reported. The diversity of MiECC systems, patients and outcomes, and the poor methodological quality of many of the randomised clinical trials (RCTs) included in these reviews, undermines the strength of this evidence and most hospitals continue to use CECC.^
9
^ Nevertheless, the potential benefit of MiECC highlights the urgent need to evaluate this technology in a large, high-quality RCT. The proposed trial will evaluate MiECC systems that conform to an established typology,^
5
^ recruit patients having the most common cardiac surgery operations, report important clinical outcomes and includes features to minimise bias.

## Methods

### Trial design and population

This COMICS trial is an international, multi-centre, randomised, controlled parallel group trial to investigate the effects of using MiECC in all patients having elective or urgent coronary artery bypass grafting (CABG), aortic valve replacement (AVR) or CABG + AVR using extracorporeal circulation without circulatory arrest (Figure 1). The trial aims to test the hypothesis that MiECC is effective and cost-effective compared to CECC for most cardiac surgery operations requiring extracorporeal circulation without circulatory arrest. The trial includes a pilot and main trial phase.

**Figure 1. fig1-0267659120946731:**
[figure not shown]
Trial schema. CABG: coronary artery bypass grafting; AVR: aortic valve replacement; CECC: conventional extracorporeal circulation; MiECC: minimally invasive extracorporeal circulation; SAE: serious adverse event.

The trial has three specific objectives:

To estimate the difference between groups in the proportion of participants experiencing the primary outcome (a composite of serious complications) up to 30 days after randomisation.To compare secondary outcomes between groups: serious adverse events (SAE; events which result in death, are life threatening, require hospitalisation or prolongation of hospitalisation, result in persistent or significant disability or incapacity) not included in the primary outcome, red blood cells (RBC) and other blood products transfused; duration of cardiac ICU and hospital stay following the index admission; resource use, generic health status.To estimate the cost-effectiveness of MiECC compared to CECC.

### Eligibility criteria

The trial is recruiting patients undergoing CABG, AVR or CABG + AVR. Cardiac surgery centres in Germany, Greece, Italy, Saudi Arabia, Switzerland, Turkey and the United Kingdom are participating. Additional centres in the United Kingdom, Germany and Canada are in set-up.

### Inclusion criteria

Patients are eligible if all the following apply:

Age ⩾18 and <85 years.Undergoing any elective or urgent CABG, AVR or CABG + AVR surgery, using extracorporeal circulation without circulatory arrest.

### Exclusion criteria

Patients are ineligible if any of the following apply:

Requirement for emergency or salvage operation.Requirement for major aortic surgery (e.g. aortic root replacement).3 Contraindication or objection (e.g. Jehovah’s Witnesses) to transfusion of blood products.Congenital or acquired platelet, RBC, or clotting disorders (patients with iron deficient anaemia only are not excluded).Inability to give informed consent for the trial (e.g. learning or language difficulties).

### Patient approach and consent

Potential trial participants are identified before their surgery from clinic lists and inpatient referrals. All potential participants receive an invitation letter and a patient information leaflet (PIL) describing the trial and are given time to discuss their participation with others outside the research team (e.g. relatives or friends) if they wish. Before their operation, patients are seen by a member of the local research team answers any questions, confirms eligibility and takes written informed consent if the patient is willing.

### Trial interventions

#### Minimally invasive extracorporeal circulation (MiECC; experimental intervention)

MiECC systems have evolved in a modular fashion, to address safety, volume and blood management issues. Systems have been classified according to their features (Types 1, II, III and IV).^
4
^ Centres may use any MiECC circuit which uses CE-marked components (or the country-specific required standards outside the European Community) and which have features consistent with Type II, III or IV criteria.

#### Conventional extracorporeal circulation (CECC; comparator intervention)

CECC should comprise (required components) standard oxygenator, roller pump, hard-cell reservoir, arterial filter, shed-blood suctions, any of a range of venting options, uncoated tubing and a cell-saver device. The following optional/alternative components can be integrated (and recorded accordingly): coated oxygenator, coated tubing and centrifugal pump. The following components are prohibited: soft-cell reservoir and vacuum-assisted venous drainage (these are advanced components which make CECC resemble a custom-made MiECC circuit).

#### Aspects of surgery common to both MiECC and CECC

Other aspects of the operations may vary by operation and centre but must be used consistently in the MiECC and CECC groups. For example, surgeons may use different cardioplegia solutions at different temperatures in different centres or for different operations. However, a surgeon carrying out one type of operation in one centre, for example, CABG in Centre A, must use the same cardioplegia solution for both MiECC and CECC. We are collecting operative details to characterise and report these variations. We believe such diversity in practice in the trial will create greater confidence in the applicability of the findings to a potential user’s clinical setting.

### Randomisation

Randomisation is performed using a secure Internet-based randomisation system, (Sealed Envelope) and is stratified by centre and surgical procedure (i.e. CABG, AVR, CABG + AVR). Participants are allocated in a 1:1 ratio to either MiECC or CECC. Randomisation takes place as close to surgery as possible and is performed by an authorised member of the local research team. Information to identify a participant and to confirm eligibility must be entered before a number is assigned (i.e. concealed randomisation).

### Blinding and other features to minimise bias

The trial includes features designed to minimise bias.^
10
^ Participants are blinded to the allocation. Documentary evidence is being sought wherever possible for events that qualify for the primary outcome; other events will be adjudicated. The 30-day primary outcome minimises loss to follow-up. Reporting bias will be minimised by a statistical analysis plan finalised before the database is locked.

### Trial outcomes

#### Primary outcome

The primary outcome is a composite of post-operative SAEs occurring up to 30 days after randomisation following the index admission. All SAEs that qualify for the primary outcome are objectively defined or will be adjudicated. The following events qualify:

(a) All-cause mortality up to 30 days after surgery(b) Myocardial infarction (MI)(c) Permanent stroke(d) Gut infarction(e) AKI (Acute kidney injury–an acute increase in serum creatinine > 26.4 μmol/L or a percentage increase in serum creatinine of more than or equal to 50%) Network criteria for stage 3 AKI^
11
^(f) Reintubation(g) Tracheostomy(h) Mechanical ventilation for >48 hours, including multiple episodes when separated by more than 12 hours(i) Reoperation(j) Percutaneous intervention(k) Sternal wound infection with dehiscence(l) Septicaemia confirmed by microbiology

Events will be documented as follows: suspected MI by serum troponin concentrations and electrocardiograph recording (ECG); stroke from brain imaging (CT or MRI) report and record of new onset focal or generalised neurological deficit; gut infraction by laparotomy or post-mortem; other events from the medical record. Equivocal events will be adjudicated.

Secondary outcomes are as follows:

(a) All-cause mortality up to 30 days after surgery(b) Other SAEs up to 30 days after surgery (primary safety outcome)(c) Units of RBC transfused up to 30 days after surgery(d) Other blood products transfused up to 30 days after surgery(e) Time to discharge from cardiac ICU during the index admission(f) Time to discharge from hospital following the index admission(g) Delirium in ICU, assessed with the Intensive Care Delirium Screening Checklist (ICDSC)^
12
^ for up to 5 days (only collected at some centres).(h) Generic health status using the EuroQol 5-level health status questionnaire (EQ-5D-5L)^
13
^ at 30 and 90 days after randomisation(i) Health resources and associated costs up to 90 days after randomisation (UK centres only)

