### Sample size

The trial is powered for the primary composite outcome. The transfusion indication threshold reduction 2 trial (TITRe2) trial, carried out in 17 UK centres, showed a rate of 15-18% in the post-operative SAEs qualifying for the primary outcome in participants receiving CECC, depending on the type of surgery received (CABG, AVR, CABG + AVR).^
14
^ Pooled estimates from previous meta-analyses of the effects of MiECC versus CECC have reported benefits of MiECC for a range of clinical outcomes: odds ratios for 30-day mortality, 0.58^
6
^ 0.40^
7
^ 0.46;^
9
^ for stroke, 0.25^
6
^ 0.40^
7
^ 0.40;^
9
^ for MI, 0.33,^
7
^ 0.40;^
9
^ for post-operative atrial fibrillation, 0.62;^
9
^ renal dysfunction 0.47.^
9
^ A smaller but still clinically important target relative difference, that is, risk ratio of 0.75, was chosen for the trial. In order to detect a risk ratio of ⩽0.75 with 90% power and 5% significance (two-tailed), 2,504 to 3,258 participants are required, depending on the numbers recruited to different surgical strata. We propose to recruit 3,500 participants to allow for uncertainty in the assumptions underpinning this calculation.

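### The AKI item of the primary composite prints two event rules that disagree, a general creatinine threshold and a restriction to stage 3, and the article does not say which one makes a patient an event

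*Protocol article*

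**What the plan says.** Item (e) under Primary outcome gives AKI a parenthesis, "an acute increase in serum creatinine > 26.4 μmol/L or a percentage increase in serum creatinine of more than or equal to 50" per cent, followed at once by "Network criteria for stage 3 AKI" and a literature reference, so that the join reads "a percentage increase in serum creatinine of more than or equal to 50%) Network criteria for stage 3 AKI". No numerical values for stage 3 are printed anywhere in the article.

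The same section says that "All SAEs that qualify for the primary outcome are objectively defined or will be adjudicated". It then gives documentation rules for MI, stroke and gut infarction. AKI has no rule of its own and falls under the remainder: "other events from the medical record. Equivocal events will be adjudicated".

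The objectives describe the endpoint as "the primary outcome (a composite of serious complications", and the abstract says it has 12 components. Under Sample size, an earlier trial "showed a rate of 15-18% in the post-operative SAEs qualifying for the primary outcome in participants receiving CECC". The target effect, a "risk ratio of 0.75, was chosen for the trial", is applied to that rate.

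**The concern.** An event definition has to sort every patient the same way whoever reads it. Here two readers can each follow the text and disagree. One applies the printed numbers and counts any creatinine rise above the threshold. The other applies the stage restriction and counts severe cases only.

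Under the first reading, creatinine rises below stage 3 enter an endpoint that is presented as serious complications. Depending on how common they are, they could make up a large share of it, which would change what the risk ratio means. The planning rate is tied to events that qualify for the primary outcome, so it too is only as definite as the AKI item. The trial was already recruiting in ten centres, with 603 patients randomised at the status date.

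**Working it through.** **Step 1. The two rules side by side.**

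| Patient | Printed threshold | Stage 3 restriction |
|---|---|---|
| Below the threshold | not an event | not an event |
| Meets the threshold, does not reach stage 3 | event | not an event |
| Reaches stage 3 | event | event |

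The rules differ in the middle row. The table takes them as nested: the parenthesis is worded as the definition of AKI, and a third stage implies lower ones. The content of the stage 3 criteria is in a cited source that is not shown, and the argument does not depend on the exact values.

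**Step 2. Whether other text decides it.** Adjudication covers equivocal events only, and a recorded 50% rise is not equivocal to someone applying the printed number. The medical-record rule says where to look, not what to count. The sample size section names no AKI threshold. Nothing settles the question.

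**Step 3. The plan's own sample size.** Inputs: control rate 15-18%, risk ratio 0.75, 90% power, two-sided 5%, 1:1 allocation. The standard pooled two-proportion formula gives a total of 3,404 at 15% and 2,750 at 18%, or 3,510 and 2,840 with continuity correction. The article states 2,504 to 3,258. With continuity correction those totals match control rates of 20% and 16%. This mismatch is a separate matter and neither causes nor follows from the AKI wording.

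**Step 4. What the choice of rule could do to power.** AKI rates are not given, so every rate below other than the 15-18% baseline is an assumption. With n = 1,750 per arm, d = p₁ − p₂ and p̄ = (p₁ + p₂)/2,

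power = Φ{[d − 1.96·√(2p̄(1−p̄)/n)] / √[(p₁(1−p₁) + p₂(1−p₂))/n]}.

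*Baseline:* 15% v 11.25% gives 90.8%; 18% v 13.5% gives 95.5%.

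*Case A: the 15% rate counted stage 3 only, and the broad threshold adds 10 or 20 percentage points of milder AKI.* The control rate is 0.15 + e and the MiECC rate is 0.1125 + r·e, where r is the risk ratio on the added events.

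| r | e = 0.10 | e = 0.20 |
|---|---|---|
| 1.00 | 25% v 21.25%, RR 0.85, power 75% | 35% v 31.25%, RR 0.89, power 65% |
| 0.90 | 25% v 20.25%, RR 0.81, power 92% | 35% v 29.25%, RR 0.84, power 95% |
| 0.75 | 25% v 18.75%, RR 0.75, power 99.4% | 35% v 26.25%, RR 0.75, power above 99.9% |

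If milder AKI instead occurs independently of the other events, in m = 10% or 20% of all patients, and MiECC does not change it, the control rate is 1 − 0.85(1−m) = 23.5% or 32%. The MiECC rate is 1 − 0.8875(1−m) = 20.1% or 29%. The composite RR is 0.86 or 0.91, and power is 68% or 49%.

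*Case B: the 15-18% rate counted the broad threshold, and the stage 3 composite is lower.* At 12% v 9% power is 83%; at 10% v 7.5% it is 74%.

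The range from about 49% to above 99.9% comes from the assumptions, not from the documents.

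**The case against.** The best defence is that there is only one rule. Without the parenthesis, item (e) reads as AKI Network criteria for stage 3 AKI, with a reference. The parenthesis begins by spelling out the abbreviation, so it looks like a gloss. If it were the event rule, the words after it would be left as a fragment. The surrounding text points the same way: the composite is one of serious adverse events, and the objectives define those by death, threat to life, hospitalisation or its prolongation, or lasting disability. A mild, transient creatinine rise with no such consequence would not belong. The article also condenses a fuller protocol, and nothing shows that sites work from this sentence.

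Most of this stands. Stage 3 is the likely intent, and the flaw is a conflict in wording, not a proven design error. It does not clear the item, because the gloss supplies the only numbers a reader can apply, and they describe a wider event than the words beside them. This is also not detail left to another document: the article states a case rule and contradicts it.

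It is also fair to say that the sample size section describes its rate as one for qualifying events, which on its face means the same definition was used. That leaves something to confirm, not an error.

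**Conclusion.** The point holds as a conflict between two stated event rules within the primary outcome. It should be corrected because it decides who counts as an event, and the correction is cheap. That stage 3 is the intended rule is an inference from grammar and context, and the sponsor has to confirm it.

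A reader might infer three stronger things, and the documents support none of them.

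- **That the trial loses power.** Power falls in Case A only if MiECC does little or nothing for milder AKI. It rises above baseline at an assumed risk ratio of 0.90 or 0.75 on the added events. The only renal effect in the article is a pooled odds ratio of 0.47 for renal dysfunction, which gives no reason to prefer the no-effect assumption. Case B rests on invented control rates. Size and direction are both unknown.
- **That patients have been misclassified.** No data on how AKI was recorded or derived are shown.
- **That the planning rate was counted with the wrong rule.** The article does not say which AKI threshold lay behind it.

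**What to change.** 1. Reconcile item (e) so that one AKI event rule applies. If stage 3 is confirmed as the intended rule, remove the parenthesis as an event criterion and write out the stage 3 criteria from the cited source.
2. Confirm that the case report form and the outcome derivation use that rule, including for participants already randomised. Re-derive AKI status only if they do not.
3. Confirm that the 15-18% rate was counted with the same AKI rule. Restate the assumed rate and power only if it was not.

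Reporting AKI of any stage as a separate secondary outcome is optional and not needed to remove the conflict.

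The cost is one wording amendment, a check of the form and derivation, and a query to whoever holds the earlier trial's event counts. No new patients or procedures are needed.

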### Data collection

Participants are followed up twice, at 30 days and 90 days after surgery. Questions elicit information about SAEs (including readmissions) experienced since discharge up to 30 days after the date of surgery. Generic health status is assessed around both 30 and 90 days. The schedule of data collection is outlined in Table 1. Data are collected from participants or their medical records, entered into a bespoke database and stored on a secure server.

**Table 1. table1-0267659120946731:** 

	T1	T2	T3	T4	T5
Date PIS sent, date approached, age, sex, type of procedure	✓				
Eligibility check, reason for ineligibility		✓			
Consent, reason for declining		✓			
Baseline data collection		✓			
Randomisation details		✓			
Primary outcome events			✓	✓	
Blood products transfused			✓	✓	
Serious adverse events			✓	✓	
Generic health status (EQ-5D-5L)		✓		✓	✓

T1: Pre-consent (anonymised). T2: Pre-admission clinic/day before operation.

T3: During index admission. T4: 30 days. T5: 90 days.

### Sample size

The trial is powered for the primary composite outcome. The transfusion indication threshold reduction 2 trial (TITRe2) trial, carried out in 17 UK centres, showed a rate of 15-18% in the post-operative SAEs qualifying for the primary outcome in participants receiving CECC, depending on the type of surgery received (CABG, AVR, CABG + AVR).^
14
^ Pooled estimates from previous meta-analyses of the effects of MiECC versus CECC have reported benefits of MiECC for a range of clinical outcomes: odds ratios for 30-day mortality, 0.58^
6
^ 0.40^
7
^ 0.46;^
9
^ for stroke, 0.25^
6
^ 0.40^
7
^ 0.40;^
9
^ for MI, 0.33,^
7
^ 0.40;^
9
^ for post-operative atrial fibrillation, 0.62;^
9
^ renal dysfunction 0.47.^
9
^ A smaller but still clinically important target relative difference, that is, risk ratio of 0.75, was chosen for the trial. In order to detect a risk ratio of ⩽0.75 with 90% power and 5% significance (two-tailed), 2,504 to 3,258 participants are required, depending on the numbers recruited to different surgical strata. We propose to recruit 3,500 participants to allow for uncertainty in the assumptions underpinning this calculation.

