### Status of the trial

Two centres started to recruit on 08 May 2018. Ten centres are currently recruiting; another centre recruited for 14 months but stopped participating for reasons unrelated to the trial. About 40-50 patients were randomised per month from 01 April 2019 to 31 March 2020 with over 600 now randomised. About 80% of participants have had CABG only. Primary outcomes are available in the database for 85%, recognising that these may still have to be entered for recent recruits. Adherence to randomised allocation is good (99%).

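### The required sample size of 2,504 to 3,258 does not follow from the stated 15-18% CECC event rate, and the reserve in 3,500 is thinner at the low end than it appears

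*Protocol article*

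**What the plan says.** All the inputs are in the Sample size section of the protocol article, except the allocation ratio, which is under Randomisation.

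- **Control rate.** An earlier UK multi-centre trial "showed a rate of 15-18% in the post-operative SAEs qualifying for the primary outcome in participants receiving CECC", varying with the type of surgery.
- **Effect.** "A smaller but still clinically important target relative difference, that is, risk ratio of 0.75, was chosen for the trial".
- **Error rates.** "In order to detect a risk ratio of ⩽0.75 with 90% power and 5% significance (two-tailed").
- **Allocation.** "Participants are allocated in a 1:1 ratio to either MiECC or CECC".
- **Result.** "2,504 to 3,258 participants are required, depending on the numbers recruited to different surgical strata".
- **Target.** "We propose to recruit 3,500 participants to allow for uncertainty in the assumptions underpinning this calculation".

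The section names no formula, mentions no continuity correction, gives no event rate for any single stratum, and states no attrition rate. Under Status of the trial, the article adds: "About 80% of participants have had CABG only".

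**The concern.** The inputs and the result stand in one paragraph, so the result can be checked directly, and it does not follow. A range that depends on the surgical mix should run from the requirement at 18% to the requirement at 15%. The printed range lies below that at both ends.

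This matters because the target of 3,500 is justified by its distance from the range. A reader sees a reserve of 3,500 − 3,258 = 242 at the demanding end and 3,500 − 2,504 = 996 at the easy end. If the range is too low for the stated rates, so is the reader's idea of how much slack the trial has for a lower event rate or missing outcomes. The Discussion says that continuation has been reviewed by the trial committees and that main-trial funding is being sought, so the margin is likely to be relied on.

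**Working it through.** **Inputs.** Control rate p1 = 0.15 to 0.18; p2 = 0.75 × p1; two-sided 5% (z = 1.960); 90% power (z = 1.2816); 1:1 allocation.

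**Formula (per group).** With d = p1 − p2 and p̄ = (p1 + p2)/2:

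n = [1.960 × √(2p̄(1 − p̄)) + 1.2816 × √(p1(1 − p1) + p2(1 − p2))]² / d²

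Continuity-corrected: n_c = (n/4) × [1 + √(1 + 4/(n·d))]²

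Each is rounded up and doubled.

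**Reproducing the printed figures.**

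- 16% v 12%: d = 0.04, p̄ = 0.14; n = (0.96178 + 0.62783)²/0.0016 = 1,579.3; n_c = 1,628.9; total 2 × 1,629 = **3,258**.
- 20% v 15%: d = 0.05, p̄ = 0.175; n = (1.05320 + 0.68716)²/0.0025 = 1,211.5; n_c = 1,251.2; total 2 × 1,252 = **2,504**.

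Both ends are matched exactly by one standard formula at round rates, but not at the rates in the text.

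**The stated rates.**

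- 15% v 11.25%: n = (0.93597 + 0.61105)²/0.0375² = 1,701.9, total **3,404**; n_c = 1,754.8, total **3,510**.
- 18% v 13.5%: n = (1.00969 + 0.65894)²/0.045² = 1,375.0, total **2,750**; n_c = 1,419.1, total **2,840**.

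| Control rate | Total N, corrected | Total N, uncorrected |
|---|---|---|
| 15% | 3,510 | 3,404 |
| 15.6% | 3,356 | 3,254 |
| 16% | 3,258 | 3,160 |
| 18% | 2,840 | 2,750 |
| 20% | 2,504 | 2,424 |

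**Other readings tried at 15% and 18%.** Unpooled variance gives 3,398 and 2,744; log risk ratio 3,444 and 2,784; arcsine 3,392 and 2,742. Changing the stated inputs does not give the pair either: one-sided 5% gives 2,774 and 2,242; 80% power 2,544 and 2,056; 0.75 as an odds ratio 4,428 and 3,794; 15-18% as the rate over both arms 2,914 and 2,342 (3,008 and 2,420 corrected).

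**Solving back.** A total of 2,504 needs a control rate of 20.0% corrected or 19.5% uncorrected. A total of 3,258 needs 16.0% or 15.6%.

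**Power with complete data (corrected / uncorrected).**

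| N | at 15% | at 18% |
|---|---|---|
| 2,504 | 77.7% / 79.4% | 86.0% / 87.1% |
| 3,258 | 87.7% / 88.7% | 93.6% / 94.2% |
| 3,500 | 89.9% / 90.8% | 95.1% / 95.5% |

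**Reserve in 3,500.** At 15%: 3,500 − 3,510 = −10 corrected, or 3,500 − 3,404 = +96 uncorrected. At 18%: 3,500 − 2,840 = 660, or 3,500 − 2,750 = 750.

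**The case against.** **The range depends on the mix of strata.** This helps one end only. Any mix of strata at 15-18% averages 15-18%. A mix near 15.6% (uncorrected) or 16% (corrected) does give about 3,258, so the upper figure may be legitimate for some mix. No mix gives 2,504.

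**The formula is not stated.** True: the continuity correction is an inference from the exact match, however strong. The primary analysis is a generalised linear model for the risk ratio, adjusted for centre and procedure, so the uncorrected figures are at least as relevant. But the choice of formula moves the total by about 3%, while 2,504 falls short of the 18% requirement by 246 (9% of 2,750) to 336 (12% of 2,840).

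**The target is adequate anyway.** This largely stands. A reader might infer that 3,500 is wholly used up, that no allowance exists, or that the trial is underpowered. The documents do not support that. A shortfall arises only if every participant is at 15% and the correction applies, and then it is 10 participants. At 16% the corrected reserve is 242 and at 18% it is 660.

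**Recruitment is mostly CABG.** A reader might conclude from the 80% CABG share that the trial sits near 15%. No stratum-specific rate is given, so that is a guess. Nor should the 85% availability of primary outcomes be read as 15% attrition: the article says that data for recent recruits may still have to be entered.

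**Conclusion.** The printed range is wrong for the printed rates. At 15-18%, the requirement is 2,840 to 3,510 corrected or 2,750 to 3,404 uncorrected. The lower bound cannot be reached on the stated inputs. The upper bound can, but it is not the maximum: the requirement at 15% is 146 to 252 participants higher.

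The consequence is limited. The design and the target are not undermined. What changes is the margin, which almost disappears at the 15% end and remains substantial at 18%.

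This rests on a two-group comparison of proportions, a single average control rate for any mix, and complete 30-day outcomes. That 16-20% was the rate actually used is a likely explanation, not an established one; only the sponsor's original calculation can settle it.

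**What to change.** Check the original calculation, then do one of two things:

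1. If other control rates were used (apparently 16-20%), state them and reconcile them with the 15-18% attributed to the earlier trial; or
2. if 15-18% is right, restate the requirement as 2,840 to 3,510 with continuity correction, or 2,750 to 3,404 without.

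Either way, name the formula and say whether a continuity correction was applied. If 15-18% stands, add that 3,500 participants with complete data give about 90-91% power at 15% and about 95% at 18%, and that the allowance is −10 (corrected) or +96 (uncorrected) at 15% and about 660-750 at 18%.

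Keep the target of 3,500, and keep the statement that it contains an allowance, described in these terms. The cost is a few sentences; recruitment and analysis do not change.
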